#### Subjective participant experience

2.6.6

Intervention acceptability will be assessed through measures of satisfaction with the intervention, and participants’ attitudes toward the intervention (41). The specific questions included in the exit questionnaire are provided in the additional material (Additional File 4). Responses will be summarized descriptively, and overall subjective experience will be classified based on the proportion of participants reporting positive or negative perceptions on their level of enjoyment, interest and willingness to engage in future interventions and adverse effects with a predefined threshold (e.g., >50% positive responses) used to indicate an overall favorable experience. Finally, the survey concludes with an open-ended question allowing participants to comment on preferred changes to the protocol that may encourage adherence, providing qualitative context to the quantitative ratings.

Further, prior to participants engaging in any of the intervention sessions involving physical activity, (physical training and concurrent training) the following scales will be used to assess the tolerance of the physical component of the intervention itself: (1) muscle soreness will be captured using a muscle soreness Likert scale from 0 being “A complete absence of soreness” to 6 being “A severe pain that limits my ability to move” and (2) pain will be measured separate to muscles soreness to articulate whether the participant is experienced pain, and if so, where. This will be captured using a visual analogue scale ranging from 0 implying no pain and 10 being worst possible pain. We are particularly interested in pain in the lower body given the nature of the intervention arms involved in physical training. Participants will be asked to provide a score of the two above scales specifically in response to the previous physical or concurrent training session.

Reporting physical and cognitive activity outside of the intervention for those within the intervention itself will also be captured pre-, mid-, and post- intervention by training staff. Physical activity behaviours will be captured using the International Physical Activity Questionnaire. Cognitive activity is noted from questions including whether they engage in any individual cognitive activities, cognitive activities with others, have occupational cognitive demands or are caring for others. This will help inform the subjective acceptability of the intervention alongside participants’ external life activity.

#### Cognitive function

2.6.7

The benefit likelihood on cognitive function will be assessed pre- and post-intervention in a single sitting, with participants located individually in a quiet room with minimal distractions. Potential harm will be defined as negative effect sizes consistently across most cognitive outcomes, clearly favoring the control group. Participants will be seated with a laptop and mouse at an individual desk and will be instructed to perform the tasks as quickly and accurately as possible. All tasks were downloaded on 6th April 2022 from the Millisecond (Seattle, USA) test library using the Inquisit Player version 6.5.2 and will be delivered in English (42). Some modifications to the base scripts will be made to be more suitable for this population including changes in timings, trial number, and colloquial understandings. Each assessment will include a series of practice trials to be completed before test trials. The cognitive battery takes ~50 min to complete and consists of five tasks in the cognitive domains that have been reported to potentially be impacted by ADT including visuospatial skills, spatial memory, and executive functioning (10). Such domains may also be responsive to concurrent training (28). Category Switch will be the first assessment and will assess executive function through a divided attention task (43). This will be followed by the Visual Simon task assessing executive function, working memory and inhibition (44). The next assessment will be the Groton Maze test assessing immediate and short-term visuospatial memory (45). The second last assessment will be the Visual Search task (Divided Attention) which is a divided attention task assessing visuospatial skills and spatial memory (46). Lastly, the Psychomotor Vigilance test assesses attention, response speed and motor co-ordination (47).

Visuospatial awareness (and fine motor skills) will also be assessed with the Purdue Pegboard. It involves the participant placing as many small pegs as possible into a pegboard in 30 s, with both their dominant hand, non-dominant hand, as well as both hands simultaneously. This assessment has specifically been included as visuomotor slowing has been shown in those with advanced prostate cancer (McGinty et al., 2014; Salminen et al., 2004) and may be sensitive to physical activity.

Given the awareness of subjective cognitive complaints, perceived cognitive functioning will be assessed subjectively through the Functional Assessment of Cancer Therapy—Cognitive Function (48). The FACT-Cog is comprised of four subscales: perceived cognitive impairments; perceived cognitive abilities; impact of perceived cognitive impairment on quality of life; and comments from others on cognitive function.

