Benefit likelihood	If results suggest likely harm across most cognitive outcomes (e.g., Consistent negative effect sizes)	Results suggest potential harm. Consider changes to protocol.	Results are neutral or positive in effect size across most cognitive outcomes. Proceed to larger trial.

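### One pattern of cognitive results, consistently negative effect sizes across most outcomes, falls under both 'do not progress' and 'progress with revisions'

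*Protocol article*

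**What the plan says.** Section 2.6.1 makes the feasibility measures the primary outcomes and says that they form the progression criteria. Table 1 in section 2.6.2 lists five criteria. The Benefit likelihood row is the only one that uses cognitive data. Its three cells read:

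- Not to progress: "If results suggest likely harm across most cognitive outcomes (e.g., Consistent negative effect sizes".
- Potentially progress with revisions: "Results suggest potential harm. Consider changes to protocol".
- Progress: "Results are neutral or positive in effect size across most cognitive outcomes. Proceed to larger trial".

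Section 2.6.7 then defines the term used in the middle cell: "Potential harm will be defined as negative effect sizes consistently across most cognitive outcomes, clearly favoring the control group".

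Two other passages bear on this. Section 2.6.2 says that mixed findings are read holistically across criteria, with safety and acceptability given priority. Section 2.7 labels effect sizes as small, moderate and large at 0.2, 0.5 and 0.8, but does not link these labels to the Benefit likelihood row.

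**The concern.** The definition of the middle column is, in substance, the example given for the left column. Suppose the concurrent arm does worse than control on most cognitive tests. One reader could cite section 2.6.7 and recommend revising the protocol; another could cite Table 1 and recommend not progressing. Both would be following the text.

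The Abstract and the Background promise assessment against preset criteria. For this row, the choice between two of the three verdicts would in practice be made after the data are seen. The row carries the protocol's no-cognitive-harm principle, and the protocol says that safety takes priority when findings are mixed, so the row should give one answer.

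**Working it through.** **Step 1. The wording side by side.**

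| Feature | Table 1, likely harm | Section 2.6.7, potential harm |
|---|---|---|
| Direction | negative effect sizes | negative effect sizes |
| Regularity | consistent (given as an example) | consistently |
| Breadth | most cognitive outcomes | most cognitive outcomes |
| Comparator | not named | control group |
| Strength | no further wording | clearly favours control |
| Verdict | do not progress | progress with revisions |

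Any result that meets section 2.6.7 also meets the Table 1 example. The only difference in strength runs the wrong way, because the more demanding description carries the milder verdict. A result that is negative on some tests but not on most has no evident cell either. It does not meet the section 2.6.7 definition of potential harm, and it need not be neutral or positive on most outcomes.

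**Step 2. Does other text settle it?** The holistic rule concerns how criteria are weighed together; it does not place a result within a row. The 0.2/0.5/0.8 labels are not tied to the row. Consistently, most, clearly and neutral have no numerical meaning.

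**Step 3. How much depends on the unquantified words?** The protocol gives no error rate for this criterion, so there is no figure to reproduce. What follows is illustrative.

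Inputs from the protocol:
- 19 per arm (section 2.4).
- The planning effect d = 0.24 (section 2.4), used here as the size of a true harm.
- The number of outcomes. The computerised battery "consists of five tasks in the cognitive domains that have been reported to potentially be impacted by ADT", and the pegboard makes six objective tests. FACT-Cog makes seven as one score, or ten if its four subscales are counted separately.

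Assumptions:
- Normal, equally correlated effect estimates, with inter-outcome correlation from 0 to 0.7 (the protocol states none).
- One comparison with control.
- Complete data.
- SE of d = √(2/19) = 0.324.

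With no true effect, each sign is negative with probability 1/2, whatever the sample size. For six independent outcomes:
- P(at least 4 negative) = (15 + 6 + 1)/64 = 22/64 = 34%.
- P(all 6 negative) = 1/64 = 1.6%.

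For five or seven outcomes, a bare majority is negative with probability 50% by symmetry, at any correlation. For ten it is 38–47%. All five negative has probability 1/32 = 3% if independent and 24% at correlation 0.7.

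Six outcomes, with ranges running from correlation 0 to 0.7 (correlated cases by simulation):

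| Reading of the rule | Fires with no true effect | Misses true harm of d = −0.24 on every outcome |
|---|---|---|
| At least 4 negative | 34% to 45% | 14% to 24% |
| At least 5 negative | 11% to 35% | 42% to 33% |
| All 6 negative | 1.6% to 22% | 79% to 48% |
| At least 4 below −0.2 | 5% to 20% | 56% to 50% |

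The last row and the last column depend on the SE of 0.324. An analysis that adjusts for baseline could have a smaller SE. The readings differ widely, and the protocol does not choose among them.

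**The case against.** The strongest reply is that this is a wording overlap in a pilot. Table 1 is headed as suggested criteria, mixed findings are read holistically, and sections 2.4 and 2.7 warn that estimates will be exploratory and imprecise. No single row automatically blocks or releases a larger trial, and neither reading lets the harm pattern through as a reason to progress. All of this stands and limits the consequence. It does not remove the contradiction, because a holistic judgement still needs each row to report one result.

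A reader might infer two stronger points, and the document supports neither.

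- *That the criterion is a sign count which would report harm by chance in up to half of null trials.* The text asks for effects that are consistent, that cover most outcomes and that clearly favour control, and the right-hand cell allows a neutral result, which a pure sign count cannot produce. The 34–50% range belongs to the loosest reading only.
- *That improvements on time or error scores would be counted as harm because lower is better.* Section 2.6.7 fixes direction by saying which group is favoured. The article gives no scoring metric for the computerised tasks, and metrics may properly be left to an analysis plan. What remains is small: the Table 1 cell says only negative, without a comparator or a coding direction.

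**Conclusion.** The point holds as an internal contradiction. Section 2.6.7 and Table 1 give the same pattern two verdicts on a primary progression criterion, and nothing else in the protocol says which applies. This follows from the wording alone and rests on no assumption. Its reach is limited to the choice between not progressing and progressing with revisions.

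The chance rates are secondary and conditional. With no true effect, a bare majority of negative signs has probability of about 34–50% for five to ten outcomes. Requiring every outcome to be negative gives about 2–24% for five or six outcomes. Both ranges assume inter-outcome correlations between 0 and 0.7. They show why the words need a number, not that the planned rule has any particular error rate.

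**What to change.** Before outcome data are examined, rewrite the Benefit likelihood row and the sentence in section 2.6.7 so that they use the same three definitions. These should be mutually exclusive and cover every possible result.

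1. Name the comparison in both places: concurrent training versus wait-list control.
2. State in both places that effects are coded so that negative means worse.
3. List the outcomes that count towards most.
4. Separate likely harm, potential harm and neutral/positive by a stated effect-size margin or interval instead of the sign of point estimates. The protocol's own 0.2 cut-off for small is one candidate.
5. Check that the middle band is not empty at 19 per arm.

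The last check matters. Take a mean of six standardised tests, with an assumed pre-post correlation of 0.6. The SE per test is √(2 × 2(1 − 0.6)/19) = 0.29, and the SE of the mean is 0.29 × √((1 + 5r)/6), which is 0.17 at r = 0.2 and 0.21 at r = 0.4. An upper 75% confidence limit below zero (multiplier 1.15) then needs an estimate below about −0.19 or −0.24. If the middle band were an estimate below −0.2 with an interval that includes zero, it would be empty in the first case and 0.04 wide in the second. A true harm of d = −0.24 would then be placed under progress in about 39–42% of trials. A composite score is therefore optional and does not by itself solve the problem.

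The cost is one table row, one sentence and a short check of the chosen bands. The downside is that a stricter margin or interval lowers false alarms but misses true harm more often at this sample size. The protocol should state that trade-off and still report each test individually.

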#### Secondary outcomes

2.6.8

Secondary outcomes will include measures of fatigue, quality of life, cardiorespiratory fitness, neurodegeneration blood biomarkers, and anthropometric measures assessed pre- and post- intervention.

#### Fatigue

2.6.9

Fatigue is commonly reported in men with prostate cancer and represents a response, and potential side-effect of the intervention. As such, it will be assessed though several means. As an overall intervention outcome, fatigue will be evaluated using the Short-Form 12 (49), including the vitality subscale questions, which will capture subjective general fatigue, pre-intervention, mid-intervention (end of Week 4) and post-intervention.

The NASA Task Load Index will also be employed for participants in all intervention groups for both sessions in Week 1 and Week 8 to provide insight into the perceived mental workload experienced by the participants. The individual dimensions of the NASA Task Load Index will be analysed separately, as research recommends (50). Rate of Perceived Exertion (RPE) will be captured during each of the physical or concurrent training sessions as a measure of perceived physiological fatigue (51).

Further, we anticipate that fatigue in response to the training intervention itself (any arm) will be common, thus the following measure specifically articulates how participants are coping with the intervention. This will be captured before every intervention session (irrespective of intervention arm) using the graded scale according to the Common Terminology Criteria for Adverse Events (40) as categorized below, and reported as a secondary outcome rather than an adverse event:

Grade 1: Fatigue relieved by rest.Grade 2: Fatigue not relieved by rest; limiting instrumental activities of daily living.Grade 3: Fatigue not relieved by rest; limiting self-care activities of daily living.

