### Intervention

2.5

The training interventions will consist of 2 sessions per week for 8 weeks conducted on non-consecutive days. Irrespective of intervention arm (not including the wait-list control), in Week 1, participants start with 2 × 30-min sessions, then 2 × 45-min sessions in Week 2, followed by 2 × 60-min sessions from Week 3 onwards (inclusive of warm up and cool down), to allow for gradual and more appropriate exposure of the training stimulus.

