#### Adherence

2.6.4

Adherence retention, and withdrawal will be recorded throughout the study, as well as study compliance. Participants will sign against attendance for training sessions and subsequent session reminders will be provided. Participants will be permitted to make up a “missed” session in the week that the session is missed, if there is time to do so (that is, reschedule a session within the same 7-day period).

Sessions throughout the course of the intervention will be booked in advance, and participants will be financially reimbursed in the form of a gift card for their time investment in the study and to assist with retention. The number of withdrawals from the study will be recorded with reasons documented (if provided).

Compliance in the sessions involving physical training, cognitive training or concurrent training will be assessed to ensure participants are meeting the parameters required of the allocated intervention. For the interventions with a physical training component, this involves ensuring participants exercise at the desired intensity (heart rate between 60 and 70% of their age-predicted heart rate maximum and/or a rate of perceived exertion that corresponds to moderate intensity on the 6–20 Borg scale (11–13) and for interventions involving cognitive training, this involves achieving the target of 20 levels per week.

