#### Adverse events

2.6.5

When a participant presents for an intervention session, before commencing training, they will be asked about the intervention subjective acceptability (detailed below), as well as whether they have experienced any adverse events in relation to the intervention. Any record of adverse events will be categorized in accordance with the Common Terminology Criteria for Adverse Events (40) as Grade 1—Mild (asymptomatic or mild symptoms; clinical or diagnostic observation only; intervention not required) through to Grade 5 (death related to adverse event).

Serious adverse events classified as events graded 3, 4 or 5 will be recorded if resulting from the administration of an intervention session within this study and will result in the modification of intervention as appropriate. Events that are serious but are not related to the intervention will not be recorded as serious adverse events. Any adverse events or safety-related withdrawals will be reviewed and managed in accordance with study protocols and relevant ethical guidelines.

Protocol modifications following an adverse event will be considered on a case-by-case basis in consultation with the clinical and medical staff involved in the study. Adverse events will be reviewed periodically, and decisions regarding continued participant involvement will be made accordingly. All intervention-related events and any resulting modifications will be reported in the final study publication.

Alternative causes such as the natural history of the underlying disease, other risk factors, and the temporal relationship of the event to the intervention are considered. The Chief Investigator will report serious adverse events related to the intervention (requiring medical or pharmaceutical intervention or hospital admission) to the University of Canberra Human Research Ethics Committee within 24 h.

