In terms of study design, the stringent exclusion criteria may prove challenging to find participants who have had at least one dose of ADT in the last 6 months and are currently undertaking it in isolation from any other treatment option (i.e., not alongside chemotherapy or radiation). However, this is intentional, as known structural brain changes and cognitive deficits associated with ADT have been shown 6 months post-treatment commencement (13). Furthermore, chemotherapy or radiation treatment separately may adversely affect cognitive function in other cancer populations (62, 63), and this study seeks to evaluate changes outside these known acute impairments on cognition possibly due to these other specific treatment types. Future trial delivery will likely need to be multi-site to increase exposure to recruitment pathways and thus participants that meet this inclusion criteria. In addition, the use of a wait-list control group may introduce attention bias, as intervention participants receive more frequent supervised contact than controls. This should be considered in the design of future definitive trials, potentially through the inclusion of an attention-matched control group.

Further, recruitment in this population has proven to be challenging with uptake as low as 17% of intended recruitment in an international exercise study in those with prostate cancer (64). Time constraints has been identified as a significant barrier to engaging in physical activity in this population (64, 65). The current study involves participants in the intervention attending the laboratory on 19 separate occasions which may influence session adherence or deter potential participants, particularly those that live further away from the research laboratory. Although we will partly address this by reimbursing participants, the aim of the study is to evaluate the effectiveness of a lifestyle intervention that would be more time efficient than its component parts. We recognize that the projected recruitment target for this study may be ambitious given the study population and intervention demands, though additional recruitment pathways will be employed to bolster the recruitment strategy periodically, including engaging social media, traditional media outlets, and other cancer related services.

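### The session-level fatigue grade is taken only at sessions that take place, so if fatigue keeps men away the recorded share at grade 2 or above is too low

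*Protocol article*

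**What the plan says.** All references are to the protocol article.

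- **Expected frequency (Section 2.6.9, Fatigue).** The article says "we anticipate that fatigue in response to the training intervention itself (any arm) will be common". It introduces a CTCAE-based grade as the measure of how men cope with the training.
- **Timing (Section 2.6.9).** "This will be captured before every intervention session (irrespective of intervention arm) using the graded scale". No other occasion for the grade is given.
- **Reporting (Section 2.6.9).** The grade is "reported as a secondary outcome rather than an adverse event".
- **Scale (Section 2.6.9).** Grade 1 is fatigue that rest relieves. Grades 2 and 3 persist despite rest and limit, respectively, instrumental daily activities and self-care.
- **Pre-session questioning (Section 2.6.5, Adverse events).** It depends on attendance: "When a participant presents for an intervention session, before commencing training, they will be asked about the intervention subjective acceptability". The adverse-event question is put at the same moment.
- **Missed sessions (Section 2.6.4, Adherence).** If there is time, a man may "reschedule a session within the same 7-day period". Reasons are documented for withdrawals where given; none are mentioned for single missed or moved sessions.
- **Analysis (Section 2.7).** Fatigue outcomes go into linear mixed models that assume data missing at random. Feasibility data are reported as frequencies.

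**The concern.** Whether a grade is observed can depend on the grade itself. The higher grades are defined by limits on everyday activity and self-care, which are plausible reasons not to travel to a laboratory. The Discussion accepts that the number of visits may affect session adherence. A man who stays away because he is exhausted contributes nothing for that day. If he makes the session up later in the week and is asked how he feels on arrival, the slot is filled with a possibly lower grade and no gap is visible.

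The Background gives cancer-related fatigue as the reason it is unclear whether concurrent training can be tolerated, and Section 2.6.2 gives safety and acceptability priority when the progression criteria are mixed. A session-level fatigue measure that loses its worst days would make training look better tolerated than it was. It would also shrink the difference between a more tiring arm and a less tiring one. The comparison at stake is among the three training arms, because the wait-list arm has no sessions and so no such grade.

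**Working it through.** **Step 1: number of grades planned.** Section 2.5 states: "The training interventions will consist of 2 sessions per week for 8 weeks conducted on non-consecutive days". So 2 × 8 = 16 sessions. Adding the familiarization, pre-test and post-test visits gives 16 + 3 = 19, which agrees with the Discussion's figure ("attending the laboratory on 19 separate occasions"). With 19 men per arm (Section 2.4) and three training arms, 3 × 19 × 16 = 912 pre-session grades are planned.

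**Step 2: how many can be absent.** Absent grades per man = 16 × (1 − adherence).
- At the 65% threshold of Table 1: 16 × 0.35 = 5.6 per man, or 912 × 0.35 ≈ 319 in all.
- At 80%: 3.2 per man.
- At 90%: 1.6 per man.

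**Step 3: effect of selective absence.** The article gives no fatigue rate and no missed-session rate, so the following inputs are assumptions. Let p be the true share of booked days at grade 2 or above, c1 the chance of missing such a day, and c0 the chance of missing any other day. Without make-ups:

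attendance = p(1 − c1) + (1 − p)(1 − c0)

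recorded share = p(1 − c1) / attendance

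With p = 0.20:

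| c1 | c0 | attendance | recorded share |
|---|---|---|---|
| 0.10 | 0.10 | 0.90 | 0.18/0.90 = 20.0% |
| 0.30 | 0.05 | 0.14 + 0.76 = 0.90 | 0.14/0.90 = 15.6% |
| 0.30 | 0.10 | 0.14 + 0.72 = 0.86 | 0.14/0.86 = 16.3% |
| 0.50 | 0.05 | 0.10 + 0.76 = 0.86 | 0.10/0.86 = 11.6% |
| 0.50 | 0.10 | 0.10 + 0.72 = 0.82 | 0.10/0.82 = 12.2% |

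The first row shows no bias when absence is unrelated to fatigue. Whenever c1 exceeds c0, the recorded share is below the true one.

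**Step 4: difference between arms.** Same formula, true shares 30% and 15%:

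| c1 | c0 | recorded | difference (true: 15 points) |
|---|---|---|---|
| 0.30 | 0.05 | 24.0% v 11.5% | 12.5 |
| 0.30 | 0.10 | 25.0% v 12.1% | 12.9 |
| 0.50 | 0.05 | 18.4% v 8.5% | 9.9 |
| 0.50 | 0.10 | 19.2% v 8.9% | 10.3 |

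The ratio stays slightly above 2 throughout.

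**Step 5: make-ups, if the grade describes the moment of arrival.** Take p = 0.20 and c0 = 0.10, with half of missed sessions made up and every made-up grade below 2.
- c1 = 0.30: made-up sessions are 0.5 × (0.06 + 0.08) = 0.07, so attendance is 0.93 and the recorded share 0.14/0.93 = 15.1%.
- c1 = 0.50: made-up sessions are 0.5 × (0.10 + 0.08) = 0.09, so attendance is 0.91 and the recorded share 0.10/0.91 = 11.0%.

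Make-ups then lower the recorded share by about one further point.

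**Step 6: does the analysis repair it?** Absence caused by that day's unrecorded fatigue is not missing at random given the observed grades, so the mixed model does not remove the bias. Simple frequencies over attended sessions do not either.

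**The case against.** The strongest objection is the recall window. Section 2.6.9 describes fatigue in response to training. The soreness and pain scales in Section 2.6.6 explicitly refer back to the previous session, and the grade definitions describe days at home more than an instant in the laboratory. If the fatigue question also looks back, the next attended session, including a make-up, recovers much of what was lost, and the loss falls mainly on men who stop coming. That stands as a limit: the article states no window for this grade, so a reader cannot conclude that a moved session always yields a recovered grade. Grades 2 and 3 also persist despite rest by definition, which makes full recovery within days doubtful, although persistent fatigue can equally mean repeated absence.

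A reader might also infer three stronger things that the documents do not support.

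- **That the make-up rule keeps adherence above its threshold.** Under the assumed rates of Step 3, attendance is already 82-90% without make-ups, well above 65%. The article does not say how a made-up session is scored.
- **That differences between arms are halved.** This needs 50% of fatigued sessions moved, complete recovery and no other absences (30% v 15% recorded as 15% v 7.5%). It is a worst case, and even there the ratio is unchanged.
- **That fatigue is recorded nowhere else.** SF-12 with vitality is taken before, midway and after, the exit survey covers adverse effects, and the adverse-event row of Table 1 names increased fatigue as an example. The first two do not depend on attending a training session. None of the three identifies fatigue as the cause of a missed session, and the adverse-event question is itself put to men who present for a session.

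Finally, this is a condensed article, and a full protocol may log reasons for missed sessions. The point therefore rests on the timing rule that the article does state, not on the absence of a log field.

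**Conclusion.** The point holds in a conditional form. As written, the session-level fatigue grade exists only for sessions that take place. If fatigue raises the chance of absence, the recorded share at grade 2 or above is biased low, and the planned analysis does not correct this. The grade definitions make such a link plausible, but the documents give no rate, so the true size is unknown and may be zero.

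Under the assumed absence rates of Step 3, a true 20% is recorded as about 12-16%, and a true 15-point contrast as about 10-13 points. These are shares of sessions. A worst grade per man would be affected less where a man has several bad days, since one recorded day is enough. A look-back question would reduce the loss further, though not after withdrawal.

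The grade is a secondary outcome and not itself a Table 1 criterion. The change is still worth making before data are collected, because booked-day grades cannot be reliably recovered afterwards.

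**What to change.** - Obtain a fatigue grade for every booked session. Section 2.6.4 says sessions are booked in advance, so the denominator exists.
- When a session is missed or moved, ask at the contact that rebooks it for the grade on the booked day and whether fatigue was the reason.
- State the recall window: the pre-session question should cover the worst fatigue since the last session.
- Report by arm the proportion of men whose worst grade over booked sessions is 2 or above, and beside it the number of sessions missed or moved for fatigue.
- Add a sensitivity count that scores fatigue-caused absences with no grade as grade 2 or above.

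The cost is two questions at an existing contact and one field in the session log. Some grades will be taken by phone instead of in person, and the fatigue figure may look slightly less favourable. The training schedule and the make-up rule are unchanged.
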